## Introduction

Dental phobia, a persistent and excessive fear of dental stimuli and procedures that results in avoidance or distress, represents a significant barrier to children and adult oral health [1]. Dental anxiety correlates positively with disadvantageous oral health behaviors and outcomes, including less frequent dental care visits [2, 3], lack of adherence to dentist advocated treatment [4], and increased likelihood of tooth decay, missing teeth, and periodontal diseases [5–7]. Dental fear and anxiety relate to poor oral health, which in turn, may increase the risk for heart disease, stroke, diabetes, and poor quality of life [8–10]. As marginalized individuals in the United States (including African American and Hispanic individuals) are particularly burdened by dental anxiety and problems of oral health, the study of dental anxiety has broad societal significance [11, 12].

Research suggests that direct associative conditioning is often responsible for the development of dental fear [13–15]. That is, an individual who undergoes an uncomfortable or painful dental procedure (unconditioned stimulus) may form an association between the dentist and/or dental-related stimuli (the conditioned stimulus) with fear (the conditioned response). In subsequent situations, such as future dental consultations, the dentist and/or dental related stimuli will then elicit the conditioned response.

Although experiencing painful or distressing dental events increases the likelihood of dental anxiety, this associative conditioning effect does not always occur. Research suggests that the experience of non-painful or non-traumatic dental events prior to negative dental experience(s) decreases the probability of enduring dental anxiety from associative conditioning [13, 14]. That is, pre-exposure to the dentist or dental related stimuli (e.g., office, chair, instruments) in the absence of a negative experience may reduce the likelihood of developing dental phobia. This impairment of associative learning from non-reinforced stimulus pre-exposure is a phenomenon labeled latent inhibition (LI). In LI, previous uneventful stimulus exposure reduces one’s ability to subsequently acquire or express a new association with that stimulus [16, 17].

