## Research hypotheses

The proposed experiment will assess if pre-exposure session spacing and pre-exposure in multiple contexts potentiate changes in expected relevance and visual attention to the pre-exposed stimulus, and LI of dental fear. Pain sensitivity will also be measured to test if this variable moderates the influence of the proposed mediators on LI.

### Hypothesis 1

Spaced pre-exposure sessions, compared to no spacing, will (a) increase engagement of the proposed mechanisms (expected relevance and attention), and (b) enhance LI of conditioned fear acquisition, recall, and retention.

### Hypothesis 2

Multiple context pre-exposure, as compared to pre-exposure in a single context, will (a) lead to stronger engagement of the proposed mechanisms (expected relevance and attention), and (b) enhance LI of conditioned fear acquisition, recall, and retention.

### Hypothesis 3

Greater pain sensitivity will be associated with increased engagement of the proposed mechanisms of expected relevance and attention and increased LI.

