### Design

The experiment employs a mixed research design, with two within-subject independent variables, two between-subjects independent variables, and one measured continuous variable. The within-subjects variables are stimulus type [stimulus type: pre-exposed to-be conditioned stimulus (CS^+^ _P_), non-pre-exposed to-be conditioned stimulus (CS^+^ _NP_), and an unpaired control stimulus (CS^−^)] and time [trial number]. The between-subjects variables are pre-exposure session spacing [no spacing vs. session spacing] and pre-exposure context [single context vs. multiple contexts]. Pain sensitivity will serve as a continuous moderator variable.

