### Data analysis plan

Hypotheses 1a, 2a, and 3 will be examined using SPSS software, as detailed below. Mplus software [36] will be used to address the remaining hypotheses. Note that throughout the analyses, an interaction between the two between-subjects factors is not of primary interest [19]. Rather, we anticipate that a particular combination of the groups, or the focal group, (i.e., pre-exposure with spacing and in multiple contexts) will have more favorable responses than each of the other groups. Consequently, we treat these between-subjects factors as one factor with four groups. Note that representing the four cells of the between-subjects factors in this way yields the same fit as a full between-subjects factorial model and readily enables us to assess the comparisons between the focal and other groups.

Hypothesis 1a: Spaced pre-exposure sessions, compared to no spacing, will (a) increase engagement of the proposed mechanisms (expected relevance and attention). Hypothesis 2a: Multiple context pre-exposure, as compared to pre-exposure in a single context, will (a) lead to stronger engagement of the proposed mechanisms (expected relevance and attention).

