To investigate Hypotheses 1b and 2b, we will conduct mediation analysis to estimate direct, indirect, and total effects associated with the pre-exposure groups on the distal outcomes of conditioned fear acquisition, recall, and retention. In parallel mediation models, the pre-exposure groups are hypothesized to impact the mediators (expected relevance and attention), which, in turn, are hypothesized to affect a given fear outcome. Note that these path models do not include within-subjects variables as the scores for the mediating variables will be obtained from the first trial of the conditioning phase, where stimulus group differences are expected to be greatest, and scores from a given distal outcome will be computed as the average of the scores across specific trials in the recall and then retention phase. If the pre-exposure variable is found to interact with stimulus type in Hypotheses 1a or 2a, then this model will be estimated separately for each stimulus type to assess if mediation is present for each stimulus.

Parameters for the mediation analyses will be estimated in Mplus with maximum likelihood estimation and percentile bootstrapping (with 20,000 bootstrap samples), with the latter used to test for the presence of indirect effects. Bootstrapping is a recommended method for mediation analysis given that indirect effects are non-normally distributed [37–39], as each indirect effect is computed as a *product* of parameter estimates.

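### Hypotheses 1b and 2b claim enhanced latent inhibition of fear, but no planned fear analysis tests whether the CS+NP minus CS+P gap differs by group, and acquisition is named as an outcome without a score

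*Protocol article*

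**What the plan says.** The hypotheses (Research hypotheses) are that spacing and multiple contexts will each "enhance LI of conditioned fear acquisition, recall, and retention". The Introduction describes LI as impaired learning about a stimulus because it was earlier met without reinforcement. The design supplies a comparator inside every participant. Under Design, "The within-subjects variables are stimulus type" (CS+P, CS+NP and CS-) and time. Task phases and manipulations gives CS+P and CS+NP the same conditioning: 12 trials each, 75% of them with the air puff.

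The Data analysis plan divides the work by software: "Hypotheses 1a, 2a, and 3 will be examined using SPSS software", while Mplus "will be used to address the remaining hypotheses", that is, 1b and 2b. The Mplus analysis is a mediation model running from pre-exposure group through expected relevance and attention to a fear outcome, with direct, indirect and total effects. Of these models it says that "these path models do not include within-subjects variables". If group interacts with stimulus type under Hypotheses 1a or 2a, "then this model will be estimated separately for each stimulus type to assess if mediation is present for each stimulus".

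The paragraph opens by listing acquisition, recall and retention as the distal outcomes. It then says that a distal outcome score is "computed as the average of the scores across specific trials in the recall and then retention phase".

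**The concern.** All four groups are pre-exposed to CS+P (Table 2), so no group shows how an unexposed participant would respond to that stimulus. The information is within the person: CS+NP is conditioned identically and differs from CS+P only in not having been pre-exposed. Enhanced LI therefore means a wider CS+NP minus CS+P gap in fear. Without a test of that gap, a group effect on fear cannot be separated from a group difference that applies to every stimulus.

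Such a difference is plausible for spacing. Spaced arms reach conditioning at session 2, at least 7 days after the cold pressor test and after an earlier session in the headset and mouthpiece. Unspaced arms are conditioned on the same day as those procedures. Familiarity or residual stress could move fear to all three stimuli together.

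Acquisition is a second, separate matter. It is one of three hypothesised outcomes, and the scoring sentence leaves it out.

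**Working it through.** **1. Which planned models contain stimulus type, and what is their dependent variable?**

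| Hypothesis | Model | Dependent variable | Stimulus type in the model |
|---|---|---|---|
| 1a, 2a, pre-exposure phase | group × trial | the two mediators | no (only CS+P is shown) |
| 1a, 2a, conditioning phase | group × stimulus × trial | the two mediators | yes |
| 3 | the above with pain sensitivity added | the two mediators | as above |
| 1b, 2b | path model | fear | no |
| 1b, 2b, after a mediator interaction | one path model per stimulus | fear | no contrast between stimuli |

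Fear is never the dependent variable of a model that compares stimuli. The per-stimulus models depend on an interaction in the mediators, not in fear. A significant result for CS+P beside a non-significant one for CS+NP is not a test of their difference.

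**2. The plan's own figure.** The sample size for 1b and 2b is 106, for an indirect effect of 0.15 = 0.5 × 0.3. Two-sided α = 0.05 is assumed, because none is given for this calculation.

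N = (1.960 + 0.842)² × (1 − 0.3²) / [0.3² × (1 − 0.5²)] = 7.849 × 0.91 / 0.0675 = 105.8, so 106.

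The figure reproduces. It powers an indirect effect on one outcome score, not a group × stimulus effect on fear.

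**3. Size of the specificity problem.** Inputs: 180 participants in four groups, so 45 per group if allocation is equal (assumed). The plan compares the focal group with each other group, so 45 vs 45. Suppose one group is lower by d SD on fear to every stimulus, and LI is the same in both. With two-sided α = 0.05 and λ = d × √(45/2), the probability of significance is Φ(λ − 1.96) + Φ(−λ − 1.96).

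| Assumed shift d | λ | P(significant), CS+P-only score |
|---|---|---|
| 0.1 | 0.47 | 0.08 |
| 0.2 | 0.95 | 0.16 |
| 0.3 | 1.42 | 0.30 |
| 0.5 | 2.37 | 0.66 |

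On CS+NP minus CS+P the shift cancels, and the probability stays at 0.05 for every d. A simulation of 5,000 replicates per setting (one group of 45 against the other 135, shifts of 0.3 and 0.5 SD, correlations 0.3 to 0.7) gave 0.05 to 0.06 for the difference.

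**4. Power, if scores were averaged over the three stimuli.** Assume a true 0.5 SD reduction in CS+P fear only, and a between-stimulus correlation of 0.5.

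- Three-stimulus average: (0.5/3) / √[(1 + 2 × 0.5)/3] = 0.204 SD; power 0.16 at 45 vs 45.
- Difference score: 0.5 / √[2 × (1 − 0.5)] = 0.5 SD; power 0.66. With correlation 0.3 it is 0.52, and with 0.7 it is 0.86.
- CS+P alone: 0.5 SD; power 0.66.

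At a correlation of 0.5 the difference score thus matches a CS+P-only score in power and adds specificity.

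**5. Acquisition.** The opening sentence of the mediation paragraph lists three outcomes. The scoring sentence draws outcome scores from two phases, recall and retention. The only conditioning-phase scores in the path models are the first-trial mediator scores. The two sentences contradict each other.

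**The case against.** The strongest reply is that the path models report total effects. In a CS+P model the total effect is a randomised estimate of how the manipulation changes fear to the pre-exposed stimulus. That stands. A reader might infer that a group effect in these models says nothing about LI, and the documents do not support so strong a reading. The effect is informative but not specific.

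The per-stimulus models would also cover CS+NP and CS-, so a general shift could be noticed there. This is partly right, and nothing in the plan says those results would be ignored. But the models are conditional on the mediators and give no formal comparison.

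The visit-schedule argument has limits too. Table 2 gives both context arms within a spacing level the same schedule, so it does not reach context comparisons made within a spacing level. Of the focal group's three comparisons, it touches the two against unspaced groups. No passage reports that such a shift occurs.

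The dilution in step 4 rests on reading the score as an average over all three stimuli. The plan speaks only of specific trials and does not say this. It would also need the mediator interaction to be absent, whereas the plan expects larger group differences for CS+P.

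Finally, it is tempting to say that acquisition is never analysed. The text does name it as an outcome, so what can be shown is a contradiction within one paragraph.

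An appeal to a fuller analysis plan does not remove the main point. The article is not silent here: it excludes within-subject variables from the fear models and fixes the phases from which outcomes are scored.

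**Conclusion.** The point holds in this form. As written, no planned analysis of fear tests whether the CS+NP minus CS+P gap differs by group, although Hypotheses 1b and 2b are claims about that gap. Treating the gap as the measure of LI is an operationalisation that follows from the design; the article does not give it as a formula.

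The consequence is a loss of specificity. With a 0.3 SD shift common to all stimuli and 45 per group, a CS+P-only comparison is significant about 30% of the time when LI does not differ. The range is 8% to 66% for shifts of 0.1 to 0.5 SD. The shift and the equal allocation are assumptions, and the mechanism offered for the shift applies to spaced versus unspaced comparisons only. Larger figures come from comparing 90 with 90 (0.52 for the same 0.3 SD shift), but that is not the comparison the plan states.

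Separately, acquisition is promised as an outcome and left without a score.

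**What to change.** 1. For each fear measure, make the group contrast on CS+NP minus CS+P (group × stimulus) the direct test of Hypotheses 1b and 2b, using the plan's focal-versus-other-group comparisons. Run it whether or not the mediators show an interaction.
2. Use the same CS+NP minus CS+P difference score in the mediation models. Keep the per-stimulus models as supportive.
3. Reconcile the mediation paragraph: either define a conditioning-phase fear score for acquisition, or remove acquisition from the outcomes of Hypotheses 1b and 2b.

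Full group × stimulus × trial models for every measure and phase are not needed to repair this.

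The cost is plan wording and a few extra models on data that the design already collects. The statistical price is a noisier score than CS+P alone if the between-stimulus correlation is below 0.5. In the step 4 example, at a correlation of 0.3, power is 0.52 instead of 0.66.

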After the final conditioning trial, participants will move to the fear *recall phase*, which consists of a series of 12 test trials (4 CS^+^ _P_ trials, 4 CS^+^ _NP_, and 4 CS^-^ trials). The structure of the recall phase trials will be the same as in the prior phases. Importantly, the startle UCS will not accompany any of the alien stimuli in the fear recall phase.

Finally, all participants will return to the laboratory at least 7 days following the session that includes the conditioning phase and complete the fear *retention phase*. This phase will consist of 12 trials that have the same set up as those in the fear recall phase.

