#### Subjective indicator of fear learning

The experiment will include indicators of subjective, physiological, and behavioral fear learning. In terms of subjective fear learning, participants will provide ratings of their relaxation/anxiety after the onset of the CS^+^ _P_, CS^+^ _NP_, or CS^−^ but prior to the onset of the dental startle UCS. The measure will be displayed in the virtual reality environment and participants will use the handheld controllers to make ratings [23].

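### The retention mediation model uses no fear measured after the puffs, so loss to follow-up that depends on that fear could attenuate the indirect effect; auxiliary variables already collected would remove this at no cost

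*Protocol article*

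**What the plan says.** The Data analysis plan in the protocol article sets out the mediation models for Hypotheses 1b and 2b. In them, "the pre-exposure groups are hypothesized to impact the mediators (expected relevance and attention), which, in turn, are hypothesized to affect a given fear outcome". The timing is fixed: the "scores for the mediating variables will be obtained from the first trial of the conditioning phase", and each outcome is "computed as the average of the scores across specific trials in the recall and then retention phase". On estimation, the plan states: "Parameters for the mediation analyses will be estimated in Mplus with maximum likelihood estimation", with a percentile bootstrap for the indirect effects. No covariate, conditioning-phase fear score or auxiliary variable is named. If group is found to interact with stimulus type, "then this model will be estimated separately for each stimulus type to assess if mediation is present for each stimulus".

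The Procedure sections give the order of events. Ratings on a trial come after the alien appears and before the puff, which falls in the last 100 ms. Conditioning has 36 trials, 12 per stimulus, and 75% of each of the two CS+ types are paired, so there are 9 + 9 = 18 puffs. Recall follows directly in the same session. Retention is different: "all participants will return to the laboratory at least 7 days following the session that includes the conditioning phase". Under the subjective indicator of fear learning, "participants will provide ratings of their relaxation/anxiety after the onset of the CS". Fear during conditioning and at recall is therefore recorded before anyone can miss the retention visit.

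**The concern.** Maximum likelihood with missing outcomes corrects for loss only to the extent that variables in the model explain it. The retention model has group and two mediators measured at the start of conditioning. Most or all of the 18 puffs come later, and how frightening they were is recorded but not used.

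Fear-related non-return is plausible on the article's own terms. Its Introduction describes dental fear as leading to avoidance, and the sample includes children from age 6. If the more fearful people stay away, the retained sample loses the upper end of the outcome. Where the mediator also drives that fear, the slope from mediator to outcome flattens. The indirect effect is the product of that slope and the group-to-mediator path, so it shrinks with it. The outcome affected is long-term retention, which the Discussion presents as a strength of the study.

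**Working it through.** **Inputs from the article (Study participants).** Group–mediator correlation a = 0.5; standardised mediator–outcome coefficient b = 0.3; indirect effect ab = 0.15; N = 106 for power 0.80; planned N = 180. Two-sided alpha of 0.05 is assumed for this test because the article states none.

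**Step 1: reproduce the plan's figure.** For the test of b adjusted for group,

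N = (z₀.₉₇₅ + z₀.₈₀)² × (1 − b²) / [b² × (1 − a²)] = 7.849 × 0.91 / (0.09 × 0.75) = 105.8, so 106. This matches the plan.

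**Step 2: large-sample simulation.** Two million records, a = 0.5, b = 0.3, no direct effect. Post-puff fear F depends on the mediator with coefficient 0.3. F and the outcome have residual correlation 0.5 or 0.8. Loss is logistic in F. Path a is fitted on everyone and path b on those with an outcome, as maximum likelihood does when only the outcome is missing. The loss rates, loss strengths and correlations are assumptions, because the article gives none.

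| Loss mechanism | Loss | Indirect effect, model as described | Change |
|---|---|---|---|
| Odds of loss ×2 per SD of F | 5–30% | 0.149 to 0.141 | −1% to −6% |
| Odds of loss ×4 per SD of F | 5–30% | 0.146 to 0.127 | −3% to −15% |
| Exactly the most fearful leave (extreme) | 5–30% | 0.137 to 0.093 | −9% to −38% |
| F unrelated to mediator and group, any of the above | 5–30% | 0.150 | none |

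The ranges span both residual correlations. With F added as an auxiliary variable, the estimate was 0.150–0.151 in every row.

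**Step 3: trial-sized simulation.** N = 180, F–outcome residual correlation 0.6–0.8, mean indirect effect:

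| Loss | Log-odds of loss per SD of F | Full data | As described | With auxiliary |
|---|---|---|---|---|
| 14% | 0.7 | 0.149 | 0.145 | 0.149 |
| 17% | 1.2 | 0.150 | 0.139 | 0.150 |
| 17%, correlation 0.8 | 1.2 | 0.149 | 0.135 | 0.149 |
| 25% | 1.2 | 0.150 | 0.135 | 0.151 |

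Repeat runs over 14–25% loss, including weaker links between anxiety and outcome, gave 0.134–0.147. That is (0.150 − 0.147)/0.150 = 2% to (0.150 − 0.134)/0.150 = 11%. With weak correlations (0.2 at 17% loss, 0.3 at 25% loss), the estimate was about 0.143–0.148.

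**Step 4: what this does to the sample-size reserve.** Losing participants down to 106 would take 1 − 106/180 = 41%. Attenuation uses up part of that margin. In the 25% scenario b is about 0.135/0.5 = 0.27, so the Step 1 formula gives 7.849 × 0.9271 / (0.0729 × 0.75) = 133.1, or 134. That compares with 0.75 × 180 = 135 participants remaining. The reserve is nearly used up, but the target is still met.

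**Step 5: cost of the auxiliary variable.** Under purely random 20% loss, where it is not needed, the SD of the estimate was 0.049 with it and 0.051 without it.

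**The case against.** The strongest reply is that this article is a condensed protocol. Missing-data rules and auxiliary variables are commonly left to a full protocol or SAP, and naming maximum likelihood in Mplus rules none of them out. That stands: the absence of such a rule is not an error. What remains is a concrete improvement to a model that is specified.

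The effect is also modest. The sampling SD of the indirect effect is about 0.05, so a shift of 0.003–0.016 is roughly 0.1–0.3 SD. Simulated power for path b at N = 180 stayed at about 0.83–0.91 in the trial-sized scenarios. No conclusion on Hypotheses 1b or 2b is shown to be at risk. Self-rated anxiety is only one of four fear indicators, and nothing in the article supports a high correlation with approach counts, distance or skin conductance. These points stand, and they bound the size.

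A reader might infer stronger versions that the document does not support:

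- *That nothing in the model predicts the loss, and that this is why bias arises.* The opposite holds. If the fear driving loss is unrelated to group and mediator, there is no bias. Attenuation arises because the mediator is linked to that fear, so the model predicts the loss partly but not fully.
- *That bias is established.* The article gives no loss rate and no link between fear and loss.
- *That recall is affected equally.* Recall takes place in the conditioning session, so only stopping within that session could remove recall data.
- *That the mediators always precede every puff.* This is certain only for the first of the 36 trials. With one model per stimulus, another alien's puff may come first. Under a fully random order (an assumption), a CS+NP puff precedes the first CS+P trial with probability 9/21 = 43%.

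**Conclusion.** The point holds in conditional form, mainly for retention. The described model leaves out fear recorded after the puffs, although that fear could drive both non-return and the retention outcome. If non-return depends on it beyond group and first-trial mediators, and the mediators affect it as the hypotheses posit, the indirect effect is pulled toward zero. The size is about 2–11% with 14–25% loss under the assumed loss strengths and correlations. It is less for outcomes weakly tied to anxiety, and nil if the fear is unrelated to mediator and group. Much larger shrinkage (up to 38%) needs the implausibly sharp case in which exactly the most fearful 30% leave.

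The repair covers loss that acts through measured fear. Loss that depends on the unobserved retention response beyond those measures would remain uncorrected. The plan's sample size of 106 reproduces and is not in question. This is a free improvement.

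**What to change.** In the Mplus retention models for Hypotheses 1b and 2b, add two auxiliary variables as saturated correlates: mean conditioning-phase anxiety and the recall score of the same outcome. Fitting recall and retention jointly is an alternative to adding the recall score. Keep everyone who reached the first conditioning trial in the model. Leave the mediators, their timing, the paths of interest and the bootstrap as they are. Enter the auxiliaries only as correlates, not as predictors of retention, so that the indirect effect keeps its meaning.

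For recall, conditioning-phase anxiety can be added in the same way, but it matters only for participants who stop within the session.

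The cost is a few lines of Mplus code and one sentence in the analysis plan. No new data are needed, and there was no loss of precision in the check under random loss.
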